### Primary trial outcomes

• Measure of attentional bias during assessment trials of the visual probe task, as measured by the difference in median reaction time (ms) taken to respond to probes replacing smoking-related stimuli versus probes replacing neutral stimuli. This will be assessed at 4 weeks post-quit in abstinent and non-abstinent smokers across both trial arms, following recommendations of Shiffman et al. [60].

• Strength of weekly urge to smoke on the MPSS, measured up to 4 weeks post-quit in abstinent and non-abstinent smokers across both trial arms.

### Secondary trial outcomes

• Strength of weekly withdrawal symptoms on the MPSS, measured up to 4 weeks post-quit in abstinent and non-abstinent smokers across both trial arms.

• Prolonged abstinence measured and biochemically validated at 4 weeks post-quit and each follow-up using the Russell standard [39]. Criteria for the Russell standard includes a 2 week grace period from quit day, followed by smoking no more than 5 cigarettes and verification by means of exhaled CO, with a cut-off point of <10 ppm.

• Time to first lapse, with a lapse episode defined here as any smoking, even a puff [39].

### Other trial outcomes

• Feasibility of running the ARTS trial within NHS SSS assessed on the basis of:

• - Rates of response to patient invitation letters;

• - Rates of recruitment at telephone screening;

• - Rates of attendance at clinic visits;

• - Rates of drop out prior to and after randomisation.

• User acceptability as measured by ratings of perceived usefulness on a patient satisfaction questionnaire.

• Change in cue-induced cravings measured on the VAS prior to and at the end of the cue-exposure task at 4 weeks, 8 weeks, 3 months and 6 months post-quit day in abstinent and non-abstinent smokers across both trial arms.

• Measure of cognitive processing bias on the pictorial Stroop task, to assess generalisation of AR effects at 4 weeks post-quit in abstinent and non-abstinent smokers across both trial arms. Stroop bias will be measured by the difference in median reaction time taken to respond to colour-naming of smoking-related stimuli versus colour-naming of neutral stimuli.

• Measure of attentional bias towards novel untrained stimuli on the visual probe task at 4 weeks post-quit in abstinent and non-abstinent smokers across both trial arms.

• Measure of attentional bias on the visual probe task and pictorial Stroop task at 8 weeks, 3 months and 6 months to assess long term effects of AR.

• Strength of urge to smoke and withdrawal symptoms on the MPSS, measured up to 8 weeks, 3 months and 6 months to assess long term effects of AR.

### Power calculation

The sample size is based on the following. In these calculations, we assume that only quitters will continue to attend clinic and that the measures will be analysed primarily in abstinent smokers, as is standard practice with withdrawal phenomena [60].

We assume conservatively that the effect of 5 sessions of AR will be no greater than the effect of a single session. From the findings of the Attwood et al. study [26], to detect a mean reduction of 26 ms (SD = 43 ms) with 80% power and a type 1 error rate of 5%, 42 participants in each group will be required. We revised this calculation to adjust for baseline attentional bias scores. In our pilot study of AR, we found an estimated correlation coefficient of −0.13 between baseline and post-training measurements. Thus, to detect a reduction of 26 ms with the same standard deviation, power and type 1 error stated above, 42 participants are still required in each group. We expect that at least 50% of participants will reach the Russell standard abstinence criteria at 4 weeks, as the NHS services achieve greater than this, providing about 50 abstinent participants in each arm, sufficient to test this hypothesis.

The trial is an exploratory study but is powered to detect differences in urge to smoke. One study on smokers quitting on pharmacotherapy found that the mean change in urge strength between quit day and week 1 was about 0.5 points measured with the MPSS and had a standard deviation of 1.2 [61]. Another study reported that glucose reduced urge strength by 1.0 points, although this was immediately after dosing [62]. In both of these studies, MPSS urge strength was scored 0–5 [42]. We assume that if AR can reduce urge strength by 0.6 points, then 62 participants in each group will be needed to detect this with 80% power and a type 1 error rate of 5%. From the earlier study [61] we used an estimated correlation coefficient of 0.41 between quit day and post-training urge strength to adjust this power calculation. This means that to detect a 0.6 point reduction in urge strength (SD = 1.2) with 80% power and a type 1 error rate of 5%, 53 participants would be required in each group. In the first 4 weeks, when withdrawal is at its height, this implies that about 200 smokers will be needed, assuming that 60% will achieve abstinence in the first 4 weeks.

The trial is not large enough to detect the effects of AR on prolonged abstinence as several hundred participants would be needed. With a sample size of 200 smokers, if AR increased abstinence rates by 30% (RR = 1.3), we have approximately 57% power to detect a difference in the proportion abstinent, using a two-sided test with a type 1 error rate of 5% and assuming an abstinence rate of 50% in the control group.

### Loss to follow-up

Participants who fail to attend clinic and do not respond to our telephone calls will be classed as smokers for the analysis of smoking abstinence, as is standard [39]. We expect to make contact with more than 90% of people at 6 month follow-up, based on experiences of a recent trial [61]. We anticipate that the effects of AR on attentional bias and withdrawal phenomena will be analysed primarily in abstinent smokers, as recommended by Shiffman et al. (2004) [60], so defaulting from routine clinic appointments by failed quitters is not considered a threat on the integrity of the trial. We therefore do not require those participants who failed to maintain abstinence and abandoned their quit to continue to attend clinics except for reasons detailed below.

This study could give valuable information on what happens to attentional bias over time, how it is affected by training, how it is affected by resuming smoking, and whether the training effect is contingent on continued abstinence. Accordingly, we will ask all participants regardless of smoking status to attend the follow-up visits. Adequate compensation should increase the likelihood of attendance.

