**Methods/Design:**

This is a double-blind randomised controlled trial. Adult smokers attending a 7-session weekly stop smoking clinic will be randomised to either a modified visual probe task with attentional retraining or placebo training. Training will start 1 week prior to quit day and be given weekly for 5 sessions. Both groups will receive 21 mg transdermal nicotine patches for 8–12 weeks and withdrawal-orientated behavioural support for 7 sessions. Primary outcome measures are the change in attentional bias reaction time and urge to smoke on the Mood and Physical Symptoms Scale at 4 weeks post-quit. Secondary outcome measures include differences in withdrawal, time to first lapse and prolonged abstinence at 4 weeks post-quit, which will be biochemically validated at each clinic visit. Follow-up will take place at 8 weeks, 3 months and 6 months post-quit.

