### Trial procedures

Participants in both trial arms will be seen weekly in clinics from 2 weeks prior to quit day up to 4 weeks post quit day. There are ten clinic sessions in total. Randomisation takes place at the second clinic session, which initiates the first of the 5 weekly AR/PT sessions. Follow up visits take place at 8 weeks and 3 months post quit day, with a final visit arranged at 6 months. Participants will be paid £15 to complete assessments at 3 month and 6 month follow-up sessions, as these are not therapeutic encounters. Participants will be reminded to attend their appointments by telephone or text message. Staff will complete a case report form (CRF) at each clinic visit, which contains a checklist of the trial procedures.

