### Clinic Tasks

• Visual probe task

• At the baseline session and again at 4 weeks post-quit, 8 weeks, 3 months and 6 months, all participants complete the assessment version of the visual probe task. The assessment version, which will be used to measure attentional bias, comprises a total of 192 trials, presented in two blocks. Each trial begins with a fixation cross displayed in the centre of the computer screen for 500 ms. A picture pair of smoking-related and neutral pictures is then presented side-by-side on the screen for 500 ms. After this picture pair disappears, a visual probe is presented in the location formerly occupied by one of the pictures. This probe is either a circle or square. Participants are required to discriminate the identity of the probe and respond accordingly by pressing the up or down arrow keys on the keyboard as quickly as possible. There is a 500 ms interval before the next trial. Presentation of each picture-pair and probe location is counterbalanced. In all trials, the visual probe replaces the smoking-related and neutral pictures with equal frequency. At the start of the task, participants carry out 8 practice trials in which neutral picture pairs are presented first, to allow them to become familiar with the procedure.

• Each block of trials is presented in a new random order for each participant, using EPrime version 2 (Psychology Software Tools Inc., Pittsburgh PA). The task takes approximately 16 minutes. Attentional bias scores will be calculated from reaction time (RT) data; an attentional bias towards smoking cues is characterized by faster reaction times towards smoking-related pictures than neutral pictures.

• Pictorial Stroop task

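### Participants who abandon their quit are not asked back at week +4, the visit at which the attentional-bias primary outcome is to be measured in everyone

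*Protocol article*

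**What the plan says.** On attendance, the Protocol article (Loss to follow-up) states: "We therefore do not require those participants who failed to maintain abstinence and abandoned their quit to continue to attend clinics". The one exception, given in its next paragraph, is "we will ask all participants regardless of smoking status to attend the follow-up visits". Trial procedures identifies those visits: "Follow up visits take place at 8 weeks and 3 months post quit day, with a final visit arranged at 6 months". The abstract agrees: "Follow-up will take place at 8 weeks, 3 months and 6 months post-quit". The cue exposure text under Clinic Tasks also lists week 4 separately from the follow-up sessions.

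On measurement, Clinic Tasks says, for the attentional-bias measure: "At the baseline session and again at 4 weeks post-quit, 8 weeks, 3 months and 6 months, all participants complete the assessment version". Primary trial outcomes sets attentional bias at 4 weeks, and weekly urge up to 4 weeks, in both abstinent and non-abstinent smokers. Analysis promises an ANCOVA of the week +4 bias scores, first by arm and then by abstinence status, together with intention-to-treat analyses.

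On planning, the Power calculation states: "we assume that only quitters will continue to attend clinic". Loss to follow-up then reasons that, because analysis will be mainly in abstinent smokers, default by failed quitters does not threaten the trial's integrity.

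**The concern.** The time point that carries the attentional-bias primary outcome is one that relapsed participants are not asked to attend. The outcome definition needs their scores, the attendance rule lets those scores go, and the sample size is built on not having them.

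Three things are at stake. First, an intention-to-treat comparison at week +4 would rest on participants selected by an outcome that the trial hypothesises retraining may change (Aims and study questions, question 4), so randomisation would not fully protect it. Second, the comparison by abstinence status could be left with a small or self-selected non-abstinent group. Third, the stated wish to learn how resuming smoking affects attentional bias would lose its first post-training reading. An unrecorded reaction-time score cannot be recovered by a later analysis plan.

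**Working it through.** **Step 1: which rule governs week +4.** Trial procedures has participants seen weekly in clinic up to 4 weeks after quit day, and Table 1 lists week +4 as a post-quit visit with behavioural support. Follow-up is placed at 8 weeks, 3 months and 6 months in the abstract, Trial procedures and Clinic Tasks. So week +4 is a clinic visit covered by the release, and the exception does not reach it. The £15 payment is for the 3- and 6-month sessions, and no payment is tied to week +4.

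**Step 2: the plan's own figures.** Inputs come from Power calculation; two-sided 5%, 80% power, so 1.96 + 0.84 = 2.80.
- Attentional bias: n per group = 2 × (43 × 2.80 / 26)² × (1 − 0.13²) = 42.2; stated 42.
- Urge: n per group = 2 × (1.2 × 2.80 / 0.6)² × (1 − 0.41²) = 52.2, rounded up to 53; stated 53.
- Abstinence, 50% against 50% × 1.3 = 65%, 100 per arm: 57.4% power; stated about 57%.
- Abstinent per arm at 50%: 100 × 0.50 = 50; stated about 50.

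The figures reproduce to within rounding. The problem is not arithmetic.

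**Step 3: missing week +4 scores if only quitters attend.** Missing per arm = 100 × (1 − abstinence rate).

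| Abstinence, control / retraining | Missing, control | Missing, retraining | Total of 200 |
|---|---|---|---|
| 50% / 50% | 50 | 50 | 100 |
| 60% / 60% | 40 | 40 | 80 |
| 50% / 65% | 50 | 35 | 85 |

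The last row is the risk ratio of 1.3 that the plan uses to illustrate power. It gives 15 percentage points more missing data in the control arm.

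**Step 4: if some failed quitters attend anyway.** Missing fraction = (1 − abstinence) × (1 − share attending). The article gives no such share, so 25% to 50% is an assumption.
- At 50% abstinence: 0.50 × 0.75 = 37.5%, down to 0.50 × 0.50 = 25%.
- At 60% abstinence: 0.40 × 0.75 = 30%, down to 0.40 × 0.50 = 20%.

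That is 20% to 37.5% overall, or 40 to 75 of 200.

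**Step 5: what is left to analyse.** Table 1 schedules the attentional-bias assessment at baseline and then not until week +4. For a participant absent at week +4, the only earlier score is baseline. With the stated correlation of −0.13, baseline explains 0.13² = 1.7% of the variance in the post-training score, so it can hardly stand in for it. Urge is different: it is rated at every session and all weekly points enter the mixed model, so scores before dropout are kept.

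**The case against.** The strongest reply is that the rule is deliberate. It follows a cited recommendation to study withdrawal phenomena in abstinent smokers, it is built into the total of 200, the study calls itself exploratory, and everyone is invited back from 8 weeks onward. This explains the rule but does not resolve the conflict: Primary trial outcomes includes non-abstinent smokers, and Clinic Tasks says all participants complete the task at week 4. An abstinent-only analysis also conditions on something that happens after randomisation.

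Other parts of the reply stand and limit the point.

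- A reader might infer that week +4 scores will be missing in exactly those who fail. The text does not say so. It releases only those who have both failed and abandoned the attempt, and it bars nobody. Someone who misses the abstinence criteria but is still trying may attend, and someone who fails on the week +4 carbon monoxide reading is present by definition.
- A reader might infer that both primary outcomes are lost. Urge is only cut short at dropout. If dropout depends on urge already observed, the mixed model can use that information.
- A reader might try to express the damage as a share of the 0.6-point urge target. The article gives no gap between relapsers and abstainers, and that target comes from studies scored 0-5, whereas this trial rates items 1-7 and models a composite.
- How missing scores will be handled commonly belongs in an analysis plan, which is not shown. Its absence here is not counted as a fault.

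**Conclusion.** The contradiction is in the text and bears mainly on week +4 attentional bias. Up to 80-100 of 200 participants (40-50%) would have no post-training score at the primary time point. This upper bound rests on the plan's own assumptions that only quitters attend and that 50-60% are abstinent. If a quarter to a half of failed quitters came anyway (an assumption), 20-37.5% would still be missing. The loss is related to outcome, and it would be unequal between arms if retraining affects relapse: 50% against 35% at a risk ratio of 1.3, which the plan uses only to illustrate power. For urge the effect is truncation, and smaller. The size of any resulting bias in either treatment estimate cannot be derived from the article. The statement that default by failed quitters is no threat to integrity does not hold for the outcome as defined.

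**What to change.** - In Loss to follow-up, add week +4 to the visits that all randomised participants are asked to attend regardless of smoking status. For those who have abandoned the attempt, attendance would be for assessment.
- Optionally, offer the same £15 at week +4 to everyone in both arms.
- Remove the statement that default by failed quitters is not a threat to the trial's integrity.
- Reconcile Loss to follow-up with Clinic Tasks, Primary trial outcomes and Analysis, so that the attendance rule, the outcome population and the intention-to-treat commitment agree.

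Cost: a short amendment; at most 200 × £15 = £3,000 if the payment is made; and modest staff time for extra attenders. The visit, the task and the appointment reminders already exist.

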### Analysis

• Primary analyses

• Attentional bias scores on the visual probe task will be calculated by subtracting median RTs to probes that replace smoking-related pictures from median RTs to probes that replace neutral pictures, with positive scores indicating a bias towards smoking cues and negative scores indicating a bias towards neutral cues. Median RTs will be used because distributions of mean RTs are often reported as skewed [33,63]; therefore we do not need to set parameters for outlying RTs. Bias scores, as measured at 4 weeks post-quit, will be used to examine AR effects on attentional bias firstly by trial arm and secondly by abstinence status using ANCOVA. An alpha level of 0.05 will be used. These analyses will be performed using PASW Statistics 18 (SPSS, Inc., 2009, Chicago, IL, USA).

• To investigate AR effects on weekly urge to smoke, data will be analysed using a mixed effects regression model with an autoregressive variance-covariance structure, to allow for variations in craving between participants. This will enable all weekly time points to be included and modelled simultaneously. An autoregressive modelling structure takes into consideration that repeated craving measurements taken closer together in time on the same participant are likely to be more highly correlated than measurements that are taken further apart in time [64]. This modelling technique will be used for MPSS composite scores for urge to smoke (MPSS-C). Regression coefficients, p-values and 95% confidence intervals (CI) will be derived from the models. These analyses will be undertaken using Stata 12.0 (StataCorp, 2011, College Station, TX: StataCorp LP).

• Intention-to-treat analyses will be performed to account for people who drop out of treatment.

• Secondary analyses

• Effects of AR on withdrawal will be examined using the same technique stated for urge to smoke analyses, in a mixed effects regression model of composite scores for withdrawal symptoms (MPSS-M). We will control for baseline MPSS-M scores, as is standard for the MPSS [42].

• To determine the proportion of people achieving abstinence by trial arm, risk ratios (RRs) will be calculated with corresponding 95% CIs. Those reported as lost-to-follow up will be counted as non-abstinent, as is standard in the reporting of smoking cessation trials [39,65].

• Proportional hazards modelling will be used to analyse the median time to lapse by trial arm; hazard ratios (HRs) will be reported with corresponding 95% CIs. These analyses will be performed using Stata 12.0 (StataCorp, 2011, College Station, TX: StataCorp LP).

• Additional analyses

• We will adjust analyses of attentional bias scores, MPSS-C scores and MPSS-M scores for potential moderators of attentional bias, urge to smoke and withdrawal symptoms. These will include age, gender and FTND across all analyses. Pre-quit urge to smoke will also be examined in the model of attentional bias scores and pre-quit attentional bias in the models of MPSS-C and MPSS-M.

• To investigate longer-term retraining effects, we will analyse 8 week, 3 month and 6 month post-quit data for attentional bias scores using ANCOVA and mixed-effects regression models for MPSS-C scores and MPSS-M scores, as stated previously.

• To examine AR effects on cue-induced craving, VAS scores will be analysed in the same way as MPSS-C and MPSS-M scores, in mixed-effects regression models. Visual analogue scale scores will be calculated from measurements taken from a 0–100 mm scale before and after the cue exposure task, which are administered 1 week before quit day and again at 4 weeks, 8 weeks and 3 months post-quit. The difference between pre and post measurements will be calculated and the change in cue-induced craving over time will be reported.

• Generalisation of AR to other cognitive bias measures will be assessed using RT scores from the pictorial Stroop task. Stroop bias scores will be calculated by subtracting median RTs to probes that replace neutral pictures from median RTs to probes that replace smoking-related pictures. Slower RTs towards smoking-related pictures indicate a bias towards smoking cues. Again, parameters for outlying RTs do not need to be defined as median rather than mean RTs will be used. Bias scores, as measured at 4 weeks post-quit, will be used to examine AR effects on Stroop bias firstly by trial arm and secondly by abstinence status using ANCOVA.

• Similarly, we will assess whether AR generalises to untrained novel stimuli that only appear in the assessment versions of the visual probe task and not during training sessions. Attentional bias scores for the trained and untrained stimuli will therefore be analysed separately using ANCOVAs.

• Responses to the patient satisfaction questionnaire and identification of group allocation will be compared across trial arms as percentages.

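### The 53-per-arm urge sample size assumes adjustment for an earlier urge score that the primary MPSS-C model does not state, and its correlation starts at quit day, which in this trial falls after the first training session

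*Protocol article*

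**What the plan says.** **Sample size.** The Power calculation section takes a 0.6-point difference in urge strength with SD 1.2, 80% power and 5% type 1 error, and states "then 62 participants in each group will be needed to detect this". It then says "we used an estimated correlation coefficient of 0.41 between quit day and post-training urge strength to adjust this power calculation" and arrives at 53 per group. The correlation comes from an earlier study of smokers quitting on pharmacotherapy. The total of about 200 smokers follows, assuming 60% abstinence.

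**Primary model.** The Analysis section, under primary analyses, says "To investigate AR effects on weekly urge to smoke, data will be analysed using a mixed effects regression model with an autoregressive variance-covariance structure". It adds that the weekly scores are modelled together and that the outcome is the composite MPSS-C. It lists no baseline urge term.

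**Secondary model.** Withdrawal (MPSS-M) uses the same technique, with one addition: "We will control for baseline MPSS-M scores, as is standard for the MPSS".

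**Additional analyses.** The extra covariates for MPSS-C are age, gender, FTND and pre-quit attentional bias. Pre-quit urge is named only for the attentional bias model.

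**Timing.** Under Trial procedures: "Randomisation takes place at the second clinic session, which initiates the first of the 5 weekly AR/PT sessions". The Intervention group section and Table 1 place that session one week before quit day. The Measures section has the MPSS taken at the start of each session.

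**The concern.** The sample size and the primary model do not describe the same analysis. The size takes credit for a covariate, and the model that must deliver the precision does not contain it. The article itself calls baseline control standard for this scale, but states it only for the secondary outcome.

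The time point behind the correlation adds a second difficulty. Weeks −2 and −1 supply urge scores taken before any training. The quit-day score is taken after randomisation and after one session. If the analysis followed the planning calculation literally and adjusted for quit-day urge, it would condition on something the intervention may already have changed. If it used a true baseline instead, 0.41 would no longer be the relevant correlation. A pre-training score lies further in time from the outcome, and the article gives no correlation for it.

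At stake are the power of one of the two primary outcomes and freedom to choose its covariate after the data are seen.

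**Working it through.** **Inputs** (Power calculation): difference 0.6, SD 1.2, power 80%, alpha 5%, r = 0.41. Two-sided testing is stated only for the abstinence calculation and is assumed here; it reproduces the urge figures. The urge effect and SD are taken at face value.

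**1. Reproduce the plan's figures** (normal approximation).
- Unadjusted: n = 2 × [1.2 × (1.960 + 0.842) / 0.6]² = 62.8, so 63 per arm (plan: 62).
- Covariate-adjusted: 62.8 × (1 − 0.41²) = 62.8 × 0.832 = 52.2, so 53 per arm (plan: 53).
- Change score, for comparison: 62.8 × 2 × (1 − 0.41) = 74.1, so 75 per arm. This does not match.

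So 53 is a covariate-adjusted figure.

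**2. Power if the model is fitted as stated, without a baseline term, at one time point.** Power = Φ(0.6 / [1.2 × √(2/n)] − 1.96).

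| n per arm | Unadjusted, normal (t-test) | Adjusted at r = 0.41, normal |
|---|---|---|
| 53 | 73% (72%) | 81% |
| 60 (60% of 100) | 78% (78%) | 85% |

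Numbers to randomise at 60% abstinence: 2 × 53 / 0.6 = 177 with adjustment; 2 × 63 / 0.6 = 210 without.

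**3. Sensitivity to the correlation.** The pre-training correlation is not given, so these values are an assumed range, using n = 62.8 × (1 − r²).
- r = 0.2: 60.3, so 61 per arm
- r = 0.3: 57.1, so 58 per arm
- r = 0.41: 52.2, so 53 per arm

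**4. If quit-day urge were the covariate.** Assume a slope of 0.41 and that a share s of the 0.6 effect is already present at quit day. The adjusted effect is 0.6 − 0.41 × s × 0.6.

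| s | Adjusted effect | Power at 53 per arm | n per arm for 80% |
|---|---|---|---|
| 0% | 0.60 | 81% | 53 |
| 20% | 0.55 | 74% | 62 |
| 50% | 0.48 | 61% | 83 |

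At a share of 20% the gain from adjusting is already gone.

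**5. What repeated measures could recover.** For an unadjusted mean of four post-quit weeks under AR(1) correlation ρ, the variance factor is (4 + 6ρ + 4ρ² + 2ρ³)/16. At ρ = 0.41 it is 0.454, giving 29 per arm. At ρ = 0.8 it is 0.774, giving 49 per arm. Both values of ρ are assumptions.

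**The case against.** The strongest reply is that this is a condensed article, that covariates are often left to an analysis plan, and that the remark about baseline control being standard refers to the MPSS as a whole. Intended control for MPSS-C is therefore plausible. That is fair as to intent. It does not remove the mismatch: the article specifies the primary model in some detail, lists further MPSS-C covariates, and omits the one its own sample size uses.

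The second reply is that the practical loss is small, and this stands in part. About 60 per arm are planned for urge, where unadjusted power is about 78%. The model uses several weekly scores, which could bring the requirement below 53. The article did not size the trial on that basis, however.

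Three stronger readings are tempting, and the documents do not support them.
- A reader might infer that quit-day urge will be this trial's covariate. It appears only as the time point of a borrowed correlation. Nor is it certain that adjusting for it would remove effect: that happens only if one session still influences urge a week later.
- A reader might apply the 50 per arm mentioned in the same section. That figure belongs to attentional bias, at 50% abstinence.
- A reader might infer that weeks −2 and −1 enter as outcomes and dilute the arm effect. The text speaks of weekly scores without saying so, and dilution would also need a single constant arm effect across all weeks.

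**Conclusion.** The point holds as an inconsistency between the Power calculation and the primary MPSS-C model, together with a planning correlation taken from a time point that is post-randomisation in this trial. The 53 per arm depends on a covariate that the primary model does not state. Without it, about 63 per arm are needed on the plan's single-time-point basis. Against the 80% target, power falls to about 72–73% at 53 per arm and about 78% at the 60 per arm expected for urge.

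These figures assume two-sided testing, the stated effect and SD, and analysis in abstinent participants as the article plans. The consequence is moderate: it should be corrected, but it does not undermine the trial. The case for correcting it rests on the two sections disagreeing about a primary outcome, and on the remedy using scores already in the schedule.

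**What to change.** 1. State that the primary MPSS-C model adjusts for MPSS-C measured before the first training session: week −2, or the start of the week −1 session. Say that quit-day urge is not used as the baseline.
2. State that the outcomes are post-training scores, and which weeks these are.
3. Restate the urge sample size or power for a pre-training correlation, shown over an assumed range (r = 0.2: 61 per arm; 0.3: 58; 0.41: 53). Alternatively, drop the adjustment and quote the unadjusted 62–63.

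The cost is wording in the protocol or analysis plan, settled before unblinding. Table 1 already schedules the MPSS at weeks −2 and −1, so no new measurement is needed.
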